### Baseline questionnaires

All participants filled in an online questionnaire before baseline measurements were taken. In case potential participants had no access to the internet a questionnaire was sent by mail. Demographic and anthropometric variables that were collected were age, gender, body weight and length. Conditions related to risk factors for cardiovascular diseases were assessed using a series of questions according to the American College of Sports Medicine [25]. Past musculoskeletal complaints of the lower extremities and back were assessed by questions on the anatomical site and the number of days lost to work and/or sporting activities. When a musculoskeletal complaint was caused by a sporting activity it was registered as a previous sports injury. When the musculoskeletal complaint was caused by running in the past it was registered as a previous running injury. Sports participation was measured by asking whether someone was participating in sports in the past twelve months (yes/no), type of sport and mean hours of sport participation per sport a week. Furthermore a question on running experience in the past ("did you ever structurally run before") was added to assess the novelty to running.

After receiving the complete questionnaire potential participants were invited for an initial interview by an experienced sports physician at the Sportsmedicine Center of the University Medical Center Groningen. The purpose of the initial interview was to screen for cardiovascular diseases and abnormalities of lower limb and to ensure that the participants were eligible and were adequately informed about the study before signing informed consent for the GRONORUN 2 study.

### Baseline orthopaedic measurements

Hip function was measured by using a universal goniometer with arm length 30 cm from axis to tip. The internal and external range of motion of the hip was assessed with the participant supine and the tested hip and knee flexed to 90°. Knee flexion and extension ranges of motion were assessed with the participant in supine position. The goniometer was placed on the lateral aspect of the knee, with the axis of the goniometer in line with the greater trochanter and the lateral malleolus. Ankle plantar flexion and dorsi flexion were measured both with the knee fully extended and flexed to 90°. One arm of the goniometer was aligned with the fibular bone and the other with the plantar surface of the foot. Furthermore, the navicular drop was assessed by measuring the change in the height of the navicular tuberosity between a participant sitting with the subtalar joint in neutral position and standing, weight bearing with the subtalar joint in relaxed stance, as described by Brody [26]. The navicular drop is a valid method to indicate the amount of foot pronation [27]. Intratester and intertester reliability of this technique is ranging from .73 to .96 [28]. Measurements were made twice for each foot, with results being averaged. These measurements were identical to the GRONORUN 1 study [19].

### Randomization

After baseline measurements and informed consent, participants were randomly assigned to the CON or the PRECON training program.

To ensure that both groups were equal in terms of injury risk, a stratified randomization was performed based on three variables; current sporting activities, previous injuries and gender. Based on current sporting activities, there were three categories of novice runners. The first category consisted of novice runners who already were participating in a sport in which axial load i.e. running, walking or jumping, was integrated. The second category was formed by novice runners who already were participating in sporting activities without axial load, like swimming and cycling. The third and last category was formed by novice runners who did not participate in any sporting activities at baseline measurements.

In a study by Macera [1], a 74% increased risk was found in runners with a positive history of previous injuries. In this study, previous musculoskeletal complaints with an impact of activities of daily life, work or sporting activities were defined as a previous injury. Since it is not clear whether the high rate of re-injury is caused by incomplete healing of a previous injury or a biomechanical problem, a differentiation in time is made. A distinction can be made between no previous injury, injuries sustained in the last 12 months before baseline measurements and injuries sustained more than 12 months before baseline measurements. The participants were also stratified for gender because men and women differ in incidence of RRIs and localisation of these injuries [6,9]. In total eighteen strata were formed by gender, previous injury (no injuries, injury 3 till 12 months ago and injuries longer then 12 months ago) and sporting activities (no, with axial load and without axial load). From each stratum, participants were randomly allocated to intervention or control group by drawing a sealed opaque envelope. Each stratum box contained equal numbers of control and intervention envelopes.

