### Participant flow

The study design and participants flow are shown in Figure 1. A total of 500 people were interested to participate in the GRONORUN 2 study and responded to the call for novice runners. To all of those who reacted on the advertisements, an information brochure in which the study protocol was clearly described, a baseline questionnaire and an appointment at the UMCG was given. Forty four did not confirm their appointment for the initial interview nor filled in the baseline questionnaire. Of those who confirmed the appointment for the initial interview and filled in the questionnaire (n = 456), four failed to attend the initial interview. Eventually, of the 452 persons who visited the UMCG for an initial interview, 20 were excluded. Reasons for exclusion were: already participating in running (n = 11), musculoskeletal injury of lower extremities or back at baseline (n = 6) and contraindications for vigorous physical activity (n = 3). After baseline measurements and stratification, 432 participants were randomly assigned to the intervention group (n = 211) and to the control group (n = 221).

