### Statistical analyses

To evaluate the success of the randomization, baseline characteristics of participants in the CON and PRECON group were compared using 2-tailed t-tests for normally distributed continuous variables. The χ^2 ^statistic was used for discrete variables. To evaluate the effect of the PRECON program on the number of injured runners in both groups, a χ^2^-test was used. The log-rank test is used to compare the Kaplan-Meier curves of the injured runners of the PRECON group and the CON group, analyzing the difference between these two groups in the probability of an RRI at any point in time. All analyses were performed following the "intention to treat" principle. Differences were considered statistically significant at P < .05. All analyses were performed using SPSS version 16.0 (SPSS Inc, Chicago, Ill).

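### Randomisation is stratified on three injury-risk factors, but both stated treatment comparisons ignore them: the tests stay valid, slightly conservative, and lose a little power

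*Protocol article*

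**What the plan says.** Under Randomization, the protocol article states that "a stratified randomization was performed based on three variables; current sporting activities, previous injuries and gender". The stated aim is "To ensure that both groups were equal in terms of injury risk". Gender has two levels, and previous injury and sporting activity have three each: "In total eighteen strata were formed by gender, previous injury" and sporting activity. Within strata, "Each stratum box contained equal numbers of control and intervention envelopes"; the box size is not given.

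The article gives reasons for each factor. For previous injury it cites a study in which "a 74% increased risk was found in runners with a positive history of previous injuries". For gender it says that "men and women differ in incidence of RRIs and localisation of these injuries", without a figure. The Background reports that, in the group's previous trial, taking part in sport without axial loading was an important predictor of RRI, again without a figure.

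Under Outcome measures, the primary outcome is the number of RRIs, with at most one per runner, so it is binary. Under Statistical analyses, the number of injured runners is compared by a χ² test, and "The log-rank test is used to compare the Kaplan-Meier curves of the injured runners of the PRECON group and the CON group". Neither test is given strata or covariates, and neither is labelled primary, although the χ² test matches the primary outcome.

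**The concern.** The factors were chosen because they are thought to drive injury risk, and allocation was balanced on them. A comparison that then ignores them uses a variance that includes the spread of risk between strata, although the design has removed most of that spread from the difference between arms. The standard error is then slightly too large, the test slightly conservative and some power is lost.

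This is a stated choice and not detail left to an analysis plan, since the article names both tests and the software. What is at stake is efficiency. The factor levels had to be known before an envelope could be drawn, so using them needs no new data.

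**Working it through.** **1. The plan's own figure.** The article gives 360 runners (2 × 180) for 40% against 30% (a 25% relative reduction), 80% power and alpha 0.05. Two-sided:

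n per arm = [1.96·√(2 × 0.35 × 0.65) + 0.842·√(0.40 × 0.60 + 0.30 × 0.70)]² / 0.10² = (1.322 + 0.565)² / 0.01 ≈ 356.

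The stated 360 is therefore close to the number needed per arm, not in total. Power of the plain χ² test is 51% at 2 × 180 and 59% at 2 × 216 (the 432 randomised). These are the baselines for the comparison below. The shortfall itself is a separate point.

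**2. Why ignoring strata costs something.** With stratum risks p_s and mean risk p̄,

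p̄(1 − p̄) = mean of p_s(1 − p_s) + variance of p_s.

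The χ² test uses the left side. Under balanced strata the difference between arms varies only by the first term on the right. The share wasted is Var(p_s) / [p̄(1 − p̄)].

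**3. Hand check, previous injury alone.** Assume 60% have a previous injury (not given in the article) and p̄ = 0.40. Then Var(p_s) = 0.4 × 0.6 × (p₁ − p₀)² and p̄(1 − p̄) = 0.24, so the share is (p₁ − p₀)². At 432 runners the plain expected Z is 0.10 / √(2 × 0.35 × 0.65 / 216) = 2.179. The share is taken at the control mean, as an approximation.

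| Reading of 74% | p₀, p₁ | Share | Expected Z | Power, Φ(Z − 1.96) |
|---|---|---|---|---|
| Odds ratio 1.74 | 0.322, 0.452 | 1.7% | 2.179/√0.983 = 2.198 | 58.7% → 59.4% |
| Risk ratio 1.74 | 0.277, 0.482 | 4.2% | 2.179/√0.958 = 2.226 | 58.7% → 60.5% |

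**4. Simulation with all three factors.** There were 40,000 trials per setting, so each power has a standard error of about 0.25 points. Boxes held 4, 50 or a very large number of envelopes, because the size is not stated. Assumed prevalences were gender 50/50, previous injury 40/25/35% (none, recent, older) and sport 35/30/35%. The odds ratios below apply to the highest-risk level; the intermediate level takes 0.7 (injury) or 0.5 (sport) of the log odds ratio. The plain χ² test is compared with a logistic score test adjusted for main effects.

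| Odds ratios: gender / injury / sport | N = 360, plain → adjusted | N = 432, plain → adjusted | Gain (points) |
|---|---|---|---|
| 1 / 1 / 1 | 51% → 51–52% | 59% → 59% | 0.0–0.5 |
| 1.3 / 1.74 / 1.5 | 51% → 52–53% | 59% → 60% | 0.8–1.5 |
| 1.3 / 2.69 / 1.5 | 51% → 53–54% | 59% → 61% | 1.8–2.4 |
| 1.5 / 2.2 / 2.0 | 51% → 53–54% | 59–60% → 61–62% | 2.0–2.6 |
| 2 / 3 / 3 | 51% → 56% | 59–60% → 63–64% | 4.1–4.9 |

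The 2.69 row shows what a risk ratio of 1.74 becomes at a reference risk of about 32%: 0.323 × 1.74 = 0.562, and (0.562/0.438) / (0.323/0.677) ≈ 2.69.

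**5. Type I error.** The plain χ² test ran at about 0.038 to 0.052, lowest with strong factors and small boxes. The adjusted score test ran at 0.050 to 0.055, so a few tenths of a point of each gain may come from its slight liberality.

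**6. All 18 strata or main effects.** There are 432/18 = 24 runners per stratum on average. A Cochran-Mantel-Haenszel test over all 18 changed power by −1.2 to +0.8 points with no or modest factor effects, +0.5 to +1.8 with moderate ones and +2.8 to +4.1 with strong ones. Main effects need 1 + 2 + 2 = 5 parameters. The injuries expected before attrition are 0.30 × 211 + 0.40 × 221 ≈ 152, ample for that.

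**7. Log-rank.** A smaller simulation (600 trials, standard error about 2 points; 432 runners, hazard ratio 0.70) compared the plain log-rank test with one stratified on all 18 strata. Mean Z moved from 2.08 to 2.12 with factor hazard ratios up to 1.7, 1.65 and 1.35. With ratios up to 2.7, 2.2 and 1.65 it moved from 2.11 to 2.25, and power from 55% to 60%. The pattern is the same, but this did not test a Cox main-effects model.

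**The case against.** The strongest reply is that the gain is close to nil on the only figure the article supplies, and that the larger gains rest on effects it does not quantify. That stands, and it is why this is a small point. It does not remove the mismatch, because the article itself argues that the factors matter.

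Four stronger readings are tempting, and the document does not support them.

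- *The P values are wrong.* They are not: type I error is at or near nominal, and any departure of note is on the conservative side.
- *The 211 against 221 split proves that the arms differ in risk.* Had every box been emptied the arms would be equal, so some strata are uneven. The totals do not show that the mix of risk factors differs. In the simulations the standard deviation of the between-arm difference in baseline risk was 0.1 to 0.4 percentage points with boxes of 4, 0.5 to 1.3 with boxes of 50 and 0.7 to 1.7 with very large boxes.
- *The unadjusted hazard ratio is biased toward 1.* No hazard ratio is planned, and the gap between marginal and conditional hazard ratios is in any case a difference of estimand.
- *A Cox model should become the primary analysis.* That would replace a binary outcome with a hazard. Stratified randomisation does not call for it.

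It is also fair to object that much of the article is in the past tense, so a change made after the arms have been compared would be post hoc. That bears on how the fix is labelled.

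**Conclusion.** The point holds as one of efficiency. Randomisation uses three factors that the article calls prognostic, and neither stated treatment comparison uses them. The tests are valid and slightly conservative. The power given up is about 0 to 1.5 points with 74% entered as an odds ratio, about 2 points if it is a risk ratio, and 4 to 5 points if all three factors are strong. These sizes rest on assumed prevalences, assumed effects for gender and sport, and an unknown box size.

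A reader might infer that adjustment would rescue the trial's power. It would not: with modest factors, power at 432 runners moves from 59% to about 60%, against the 80% stated.

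**What to change.** - Analyse the binary primary outcome (runner injured or not) with a logistic model containing treatment and main effects of gender, previous injury (three levels) and sporting activity (three levels). Report the treatment effect with a 95% confidence interval. Do not use 18 separate strata.
- Adjust the time-to-RRI comparison for the same factors, by a Cox model with main effects or a log-rank test over a few collapsed strata, and label it secondary.
- Keep the plain χ² and log-rank tests as supportive.

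The cost is a few lines of analysis text and no new data. The model should be fixed before outcomes are compared by arm. If that comparison has already been made, report the adjusted analysis beside the stated tests and label it as added later. The sample-size shortfall needs its own correction.

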### Participant flow

The study design and participants flow are shown in Figure 1. A total of 500 people were interested to participate in the GRONORUN 2 study and responded to the call for novice runners. To all of those who reacted on the advertisements, an information brochure in which the study protocol was clearly described, a baseline questionnaire and an appointment at the UMCG was given. Forty four did not confirm their appointment for the initial interview nor filled in the baseline questionnaire. Of those who confirmed the appointment for the initial interview and filled in the questionnaire (n = 456), four failed to attend the initial interview. Eventually, of the 452 persons who visited the UMCG for an initial interview, 20 were excluded. Reasons for exclusion were: already participating in running (n = 11), musculoskeletal injury of lower extremities or back at baseline (n = 6) and contraindications for vigorous physical activity (n = 3). After baseline measurements and stratification, 432 participants were randomly assigned to the intervention group (n = 211) and to the control group (n = 221).

**Figure 1 F1:**
[figure not shown]
**Flow chart of the GRONORUN 2 study**.

### Movie: Correct hopping technique

#### Training program

##### 4-week preconditioning program

The PRECON group received a 4-week individual preconditioning training program (Table 1). This program gradually increases biomechanical load on the lower extremities with walking and hopping sessions. Participants were instructed to walk briskly on their running shoes three times a week. During two of the three walking sessions per week, participants carried out hopping exercises. After every five minutes of walking a session of hopping was carried out. In approximately half an hour six sessions of hopping were carried out. The number of hops as well as the weekly walking distance increased gradually. The PRECON group received verbal information about the correct hopping technique at the initial interview and there was a video instruction on the personalized environment of the internet based training log of the PRECON group.

**Table 1 T1:** The 4-week preconditioning (PRECON) program with walking and hopping

	PRECON training 1			PRECON training 2			PRECON training 3	Total	
	**Walk** **(min)**	**Hop**	***(rep.)***	**Walk** **(min)**	**Hop**	***(rep.)***	**Walk** **(min)**	**Walk** **(min)**	**Hop**

week 1	5	50	*(6)*	5	60	*(6)*	30	**90** **[7500 BW]**	**660** **[2310 BW]**
week 2	5	60	*(6)*	5	70	*(6)*	45	**105** **[8750 BW]**	**780** **[2730 BW]**
week 3	5	70	*(6)*	5	80	*(6)*	60	**120** **[10000 BW]**	**900** **[3150 BW]**
week 4	5	80	*(6)*	5	90	*(6)*	60	**120** **[10000 BW]**	**1020** **[3570 BW]**
week 5	Start of the 9-week training program								

The content of the PRECON training program is expressed in minutes of walking (Walk) and the number of hopping in place (Hop) and the amount of repetitions (rep.) of walking and hopping. The right column contains total minutes of walking and total performed hops each week. In the last two columns the additional load of walking and hopping each week is expressed between brackets [] in bodyweight (BW)

The correct technique of hopping in place was a relaxed standing position with a distance of approximately 30 cm between the left and right foot with both hands in the sides. Then small jumps in place were performed with the forefeet almost keeping contact with the ground (Additional file 1). During the 4 weeks of the preconditioning program of the PRECON group the CON group was instructed to do their normal exercise routine and sporting activities if applicable.

In the first training week, in which both groups are starting to run, the theoretical extra biomechanical load of running (10 km/h; total 30 min, impact 2.0 bodyweight (BW) per landing) and walking (5 km/h, total 30 min, impact 1.0 BW per landing) is approximately 12,500 extra BW. Walking is a low cyclic impact force activity and hopping is a high cyclic impact force activity. Both activities stress the body in a cyclic way, especially the lower extremities, so that the body has to positively adapt to the biomechanical stimuli.

In the first week of the PRECON program the extra biomechanical load of walking (5 km/h, total 90 min, impact 1.0 BW per landing) and hopping (660 hops, impact per hop 3.5 BW per landing) was approximately 9810 extra BW. In week 2 there is 11480 extra BW, in week 3 13150 BW and in week 4 13570 BW (Figure 2).

**Figure 2 F2:**
[figure not shown]
**Biomechanical load for the PRECON (week 1-13) and the CON (week 5-13) group**. The load of walking, hopping and running is expressed in bodyweight (BW) per week. Week 1-4 was the intervention period of the PRECON group. From week 5 both groups followed the same training program.

##### The 9-week training program

Nine weeks before the Groningen 4-Mile running event all participants were instructed to start their 9-week training program (Table 2). Participants of the CON and PRECON group received the same general written and oral information on intensity of running and on warming up and cooling down. Participants were instructed to walk briskly for 5 minutes as a warm up, and 5 minutes as cool down. Given that the best available evidence indicates that stretching before or after exercise does not prevent muscle soreness or injury [29], participants were instructed not to perform stretching exercises before, during or after the training sessions.

**Table 2 T2:** The 9-week training program for both groups

	Training 1			Training 2			Training 3			Total	
	**run**	***walk***	**(rep.)**	**run**	***Walk***	**(rep.)**	**run**	***walk***	**(rep.)**	**Run**	***walk***

week 1	**1**	*1*	(10)	**1**	*1*	(10)	**1**	*1*	(10)	**30**	*27*
week 2	**2**	*1*	(6)	**2**	*1*	(6)	**2**	1	(6)	**36**	*15*
week 3	**4**	*2*	(3)	**4**	*2*	(4)	**4**	*2*	(3)	**40**	*14*
week 4	**6**	*2*	(3)	**5**	*2*	(3)	**6**	*2*	(3)	**51**	*12*
week 5	**6**	*2*	(3)	**9**	*2*	(2)	**6**	*2*	(3)	**54**	*10*
week 6	**8**	*2*	(3)	**15**	*0*	(1)	**15**	*5*	(2)	**69**	*9*
week 7	**10**	*2*	(2)	**15**	*5*	(2)	**10**	*2*	(2)	**70**	*9*
week 8	**30**	*0*	(1)	**15**	*5*	(2)	**30**	*0*	(1)	**90**	*5*
week 9	**30**	*0*	(1)				**The Groningen running 4-Mile event**			**30**	*0*

The content of each training session is expressed in minutes of running (run), minutes of walking between the running sessions (walk) and number of repetitions (rep.). The last two columns contains the total minutes of running and walking for each week.

The frequency of running was equal in both groups. Each training week except the last week i.e. the week of the Groningen 4-Mile running event, consisted of three training sessions represented by a combination of running and walking. Participants were encouraged to run on Monday, Wednesday and Saturday or on Tuesday, Thursday and Sunday. Runners were advised to run at a comfortable pace at which they could converse without breathlessness. Both groups trained individually, without a trainer on a self-chosen course.

### Outcome measures

The primary outcome of the GRONORUN trial was the number of RRIs in both groups. A runner could only have one RRI. Definition of a RRI in this trial was; running related musculoskeletal ailment of the lower extremities or back, causing a restriction of running for at least one week, i.e. three consecutive training sessions.

Information on RRIs and exposure data was collected using an internet based running log. Each of the participants received a study number and a password to enter a personal environment of the web based training log. After each training week participants had to fill in their running activities, other sport activities and injuries.

Per training session the total minutes of running, total minutes of walking and injuries were registered. Data on injuries were collected by registering anatomical site of the body and severity of pain. Severity of pain was subdivided in pain without limitation (no RRI), pain that caused a restriction of running (scored as an RRI) and pain which made running impossible RRI (scored as an RRI). In case of skipping a training session, the reason (RRI, other injury, motivation, illness or remaining reason) for it was asked. When a "running related injury" was the reason for not training, information on anatomical site and severity was asked. To point out the anatomical site of an injury, a picture of the lower body was shown after reporting a RRI. By clicking on the anatomical site of the RRI, the same spot was appointed in red. When participants did not enter their digital training log after one week, a reminder was send by email automatically. In case of not having access to the Internet, all participants had also a hard copy of the running log.

